## Abstract

**Introduction:**

Short-term clinical outcomes from SARS-CoV-2 infection are generally favorable. However, 15–20% of patients report persistent symptoms of at least 12 weeks duration, often referred to as long COVID. Population studies have also demonstrated an increased risk of incident diabetes and cardiovascular disease at 12 months following infection. While imaging studies have identified multi-organ injury patterns in patients with recovered COVID-19, their respective contributions to the disability and morbidity of long COVID is unclear.

**Methods:**

A multicenter, observational study of 215 vaccine-naïve patients with clinically recovered COVID-19, studied at 3–6 months following infection, and 133 healthy volunteers without prior SARS-CoV-2 infection. Patients with recovered COVID-19 were screened for long COVID related symptoms and their impact on daily living. Multi-organ, multi-parametric magnetic resonance imaging (MRI) and circulating biomarkers were acquired to document sub-clinical organ pathology. All participants underwent pulmonary function, aerobic endurance (6 min walk test), cognition testing and olfaction assessment. Clinical outcomes were collected up to 1 year from infection. The primary objective of this study is to identify associations between organ injury and disability in patients with long-COVID symptoms in comparison to controls. As a secondary objective, imaging and circulating biomarkers with the potential to exacerbate cardiovascular health were characterized.

**Discussion:**

Long-term sequelae of COVID-19 are common and can result in significant disability and cardiometabolic disease. The overall goal of this project is to identify novel targets for the treatment of long COVID including mitigating the risk of incident cardiovascular disease.

**Study registration:**

clinicaltrials.gov (MOIST late cross-sectional study; NCT04525404).

## Introduction

The coronavirus disease (COVID)-19 pandemic has caused significant worldwide death and disability, particularly prior to the widespread availability of vaccine. Since the start of the pandemic, there have been seven waves of COVID-19 caused by evolving variants of the Severe Acute Respiratory Syndrome coronavirus-2 (SARS-CoV-2) (1, 2). In Canada, the province of Alberta, a region with 4.5 million inhabitants, has consistently had the highest seroprevalence for SARS-CoV-2 and in November 2023 approximately 85% had evidence for prior infection (3). However, the immediate health risk from acute infection has been low with a hospitalization rate of 5.5% and death in 1% (4).

While the short-term prognosis of COVID-19 is excellent, the intermediate and long-term health risks are of greater concern. A 2022 national survey found that approximately 17% of Canadians with COVID-19 report persistent symptoms lasting greater than 12 weeks, a syndrome referred to as long COVID or post COVID condition (5, 6). Symptoms are often characterized by fatigue, shortness of breath and/or cognitive impairment, with a disproportionate effect in women (5). Among affected individuals, 47% reported symptoms lasting at least 1 year and 21% described symptoms that often or always limited daily activities. The national survey also found that 27% of patient with SARS-CoV-2 developed long COVID following the Alpha variant infection compared to 13% with the Omicron variant (5).

Furthermore, population health studies have shown that COVID-19 confers a 50–70% excess risk of incident cardiovascular disease and diabetes mellitus in the first 12 months (7, 8). These health risks appear greater in patients with long COVID (9). The mechanism(s) responsible for long COVID and the increased cardiometabolic risk are not well understood and there is a lack of high-quality evidence-based studies guiding management.

The prevailing etiologic mechanisms proposed for long COVID include immune dysregulation, autoimmunity and immune imprinting, endothelial dysfunction and thrombosis, impaired neurological signaling and effects on the host microbiome (10). However, knowledge on pathogenesis remains limited and there is an important unmet need for rigorous preclinical and clinical studies in long COVID. Given the systemic (i.e., multi-organ) nature of both acute phase COVID-19 illness and long COVID, knowledge has been gained from whole body imaging. Magnetic resonance imaging (MRI) is a safe (non-ionizing radiation), non-invasive imaging technique that provides detailed information on tissue changes including injury. MRI has been used as an alternative to computed tomography for the characterization of pulmonary disease following severe COVID-19 pneumonia (11). MRI derived measures of visceral adipose tissue and liver fat are also strongly associated with risk of hospitalization from COVID-19 independent of body mass index (12). Whole body MRI-based studies of patients with recovered COVID-19 have identified subclinical multi-organ involvement (13–15). In an MRI study of 201 patients with long COVID, mean age 45 years, organ damage was identified in 70%, including the pancreas in 45%, liver in 29% and heart in 24% (14). In this study, MRI evidence of organ impairment was defined as a non-contrast T1 time (longitudinal relaxation time) greater than normal reference values. Several cardiac MRI based studies of patients with recovered COVID-19 have found evidence of subclinical myocardial inflammation (16–18), however, the clinical significance of this finding is not well established.

We undertook a multicenter, prospective study of patients in Alberta with recovered COVID-19 from October 2020 to August 2021 to characterize symptom burden, functional impairment and end-organ damage by MRI. We hypothesized that the extent of tissue injury on MRI would be associated with patient reported disability and objective measures of functional performance.

Our primary objective was to comprehensively apply multi-system MRI to assess the presence and extent of organ injury (heart, lungs, brain, abdominal viscera and skeletal muscle) among patients with recovered COVID-19 and compare these findings between patients with moderate to severe symptoms, minimal symptoms, and healthy controls without prior infection. As a secondary objective, we also sought to characterize imaging and circulating biomarkers with the potential to exacerbate cardiovascular health. Additionally, we incorporated opportunistic supplementary studies to explore the impact of COVID-19 on energy metabolism and patient’s perspectives.

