**Figure 1 fig1:**
[figure not shown]
Schema of study design. Upper panel depicts recruitment of patients with recovered COVID-19 and healthy controls without prior COVID-19. Middle panel depicts functional testing, blood collection and magnetic resonance imaging for all participants. Functional testing included Brief Smell Identification Testing (B-SIT), 6 min walk testing, cognitive testing on a tablet with NIH toolbox and spirometry. Bottom panel depicts collection of clinical outcomes at 12 months. CBC, complete blood count; AST, aspartate aminotransferase; ALT, alanine aminotransferase; LDH, lactate dehydrogenase; GGT, gamma-glutamyl transferase; LVEF, left ventricular ejection fraction; DTI, diffusion tensor imaging.

A detailed assessment of relevant medical history and medication use was achieved through direct questioning and a review of health records. In patients with recovered COVID-19, data on the timing and duration of illness, the need for hospitalization and transfer to intensive care were recorded.

At the time of study-related functional assessments and MRI, patients with recovered COVID-19 were screened for the presence of long COVID related symptoms including fatigue, cognitive impairment, shortness of breath, chest pain and palpitations using a standardized questionnaire. Additionally, patients rated the overall impact of these symptoms on their daily activities using a 5-point scale ranging from 1 (no limitations) to 5 (severely limited).

Blood pressure, heart rate and oxygen saturation were measured on all participants and blood work was performed to assess for circulating biomarkers of inflammation (c-reactive protein, white blood cell count with differential and d-dimer), end organ damage (high sensitivity cardiac troponin I, b-type natriuretic peptide, creatinine and hepatic enzymes) and cardiometabolic profile (glucose, insulin and lipid profile). Blood biospecimens were also stored in a research biobank (Canadian BioSample Repository) for future analysis.

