### Statistical plan

The Shapiro–Wilk normality test will be used to test the normal distribution of continuous variables which will be expressed as mean ± standard deviation or median (25th, 75th percentile), as appropriate. Categorical variables will be expressed as frequency and percentage. When comparing data between recovered COVID-19 patients and healthy controls, chi-square testing or Fisher’s exact test will be used for categorical variables and two sample t-test or Mann–Whitney U test used for continuous variables, as appropriate. Functional performance, biomarker results and imaging metrics indicative of organ injury will be compared across groups of symptom severity (none, mild, moderate and severe) within the recovered COVID-19 patients using a one-way analysis of variance with *post hoc* pairwise comparisons by either Tukey’s or Games-Howell tests, depending on equality of variances. Pearson correlation analyses will evaluate relationships between MRI measures of tissue injury and functional performance metrics. Univariable Cox proportional regression of clinical outcome will be performed in all serum and imaging parameters. In the multivariable Cox proportional hazard analysis, all non-collinear parameters of interest with univariable *p*-value < 0.2 will independently test for their association with composite outcome after adjustment for baseline risk. A *p* value less than 0.05 will be considered significant for all tests.

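### The primary objective sets symptom groups against healthy controls, but no planned test compares any symptom group with controls

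*Protocol article*

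**What the plan says.** The last paragraph of the Introduction gives the primary objective: to assess organ injury by MRI and "compare these findings between patients with moderate to severe symptoms, minimal symptoms, and healthy controls without prior infection". That is three groups, two of them patient strata. The Methods paragraph of the Abstract words the objective differently, as to "identify associations between organ injury and disability in patients with long-COVID symptoms in comparison to controls", but it too sets symptomatic patients against controls.

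The Statistical plan contains two group comparisons:

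- One begins "When comparing data between recovered COVID-19 patients and healthy controls" and uses two-sample tests on all patients together, whatever their symptoms.
- In the other, organ injury measures are "compared across groups of symptom severity (none, mild, moderate and severe) within the recovered COVID-19 patients using a one-way analysis of variance", followed by "pairwise comparisons by either Tukey’s or Games-Howell tests, depending on equality of variances".

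The remaining analyses, Pearson correlations and Cox models, do not compare these groups. On significance, the plan says only that a p "value less than 0.05 will be considered significant for all tests".

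**The concern.** The objective and the plan describe different comparisons. The severity analysis is expressly limited to patients, so controls never enter it. The only test that includes controls merges patients with and without symptoms. If organ injury tracks symptoms, as the study hypothesizes, pooling averages an effect in the symptomatic with no effect in the rest.

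At stake is the claim that readers will look for first: whether patients with moderate to severe symptoms show more organ injury than people never infected. Under the plan as written, that claim would rest either on a diluted contrast or on an analysis that was not planned.

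**Working it through.** **Step 1: contrasts required and contrasts planned.**

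| Contrast in the objective | Planned test |
|---|---|
| Moderate-severe v controls | None; only pooled patients v controls |
| Minimal v controls | None; only pooled patients v controls |
| Moderate-severe v minimal | Indirect; 4×3/2 = 6 pairwise tests among four uncollapsed levels |

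Neither of the two stratum-against-control contrasts is planned.

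**Step 2: inputs for the size of the effect.** The protocol gives no power calculation to reproduce; its targets of 200 patients and 100 controls are described as empirical. From Table 3: 215 patients and 133 controls. The significance level of 0.05 is from the Statistical plan; I take it as two-sided, which is not stated. Assumed, because the protocol gives none of these: a 0.5 SD effect only in the moderate-severe stratum, a within-group SD of 1, and a stratum share s of 20%, 30% or 50% (43, 64 or 108 patients).

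**Step 3: pooled patients v controls.** The expected difference is 0.5s, that is 0.10, 0.15 or 0.25 SD. The noncentrality is 0.5s / √(1/215 + 1/133) = 0.5s / 0.1103 = 0.91, 1.36 or 2.27. Power from the noncentral t with 346 df is 15%, 27% or 62%.

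**Step 4: moderate-severe v controls directly.** The noncentrality is 0.5 / √(1/n + 1/133) = 2.85, 3.29 or 3.86 for n = 43, 64 or 108. Power is 81%, 90% or 97%. At α = 0.05/2 = 0.025 (Bonferroni over two contrasts) it is 72%, 85% or 95%.

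**Step 5: the planned four-level ANOVA under the same assumption.** If none and mild share one mean, and moderate and severe share another, λ = 215 × s(1 − s) × 0.5² = 8.6, 11.3 or 13.4. Power from the noncentral F with 3 and 211 df is 68%, 81% or 88%.

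| Share moderate-severe | Pooled v controls | Direct v controls | Direct, Bonferroni over 2 | ANOVA within patients |
|---|---|---|---|---|
| 20% | 15% | 81% | 72% | 68% |
| 30% | 27% | 90% | 85% | 81% |
| 50% | 62% | 97% | 95% | 88% |

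**The case against.** The strongest reply is that the plan does address the study's hypothesis. The Introduction hypothesizes that tissue injury goes with reported disability and with functional performance. The within-patient ANOVA tests the first and the Pearson correlations test the second. The ANOVA also has reasonable power under the assumption used here (Step 5). This stands. A reader might infer that the plan never tests its primary question, and the document does not support that. What is missing is the comparison of symptom strata with controls, plus a direct moderate-severe v minimal contrast.

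Three other readings are tempting and also go too far:

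- **The severity groupings are incompatible.** They are not. None, mild, moderate and severe can be collapsed into minimal and moderate-severe; the collapse is simply not stated.
- **A 5-point scale contradicts a four-level analysis.** The section on medical profile and post-COVID-19 symptoms describes both a symptom questionnaire and a 5-point rating of impact on daily activities. The document does not say which one defines severity, so no contradiction is shown.
- **An ordered scale demands a trend test.** One-way ANOVA on ordered groups is valid, and a trend test's advantage depends on assuming a linear trend.

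It might also be said that a journal article leaves such details to a fuller plan. That covers cut-points. It does not cover an explicit objective and an explicit plan that disagree: the severity analysis is restricted in so many words to recovered patients.

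**Conclusion.** The concern holds for the control comparison. Neither symptom stratum named in the primary objective is compared with controls by any planned test, and moderate-severe v minimal is covered only through uncollapsed pairwise tests. This follows from the text alone.

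The power figures illustrate the cost and rest on the assumed 0.5 SD effect, its confinement to the moderate-severe stratum, and the assumed shares. On those terms, the only planned control contrast has 15% to 62% power where a direct one has 81% to 97%, or 72% to 95% after correction for two contrasts. If minimal-symptom patients were also affected, the dilution would be smaller.

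**What to change.** Make a three-group comparison (controls, minimal, moderate to severe) the primary group analysis. Name two contrasts, moderate-severe v controls and moderate-severe v minimal, under a post hoc rule that controls multiplicity. State which recorded measure defines the strata, and how the four levels become two (for example, none and mild as minimal; moderate and severe as moderate to severe). Align the Abstract, the Introduction and the Statistical plan to this wording. Keep the pooled test and the four-level ANOVA as secondary analyses.

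The change needs analysis work and wording, with no new data. Its price is somewhat lower power per contrast: in the example, 81%, 90% and 97% become 72%, 85% and 95%.

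It does not repair comparability. Under Participant selection, controls with cardiovascular disease or risk factors were excluded. Table 3 accordingly shows no hypertension, diabetes or dyslipidemia among controls, against 24%, 13% and 18% of patients. With no controls having these conditions, adjustment cannot separate them from prior infection, and the report should say so for every contrast with controls.

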## Methods and analysis

### Study design

This is an observational prospective case–control study of patients in Alberta with recovered COVID-19 from the first 2 waves of the pandemic and age- and sex-matched healthy control participants without prior COVID-19 infection. Institutional approval was obtained from the health research ethics boards at the University of Alberta for the study of patients with recovered COVID-19 (Pro00102389), the two supplementary studies (Pro00109391, Pro00110221) and the healthy controls (Pro00110706) and at the University of Calgary for patients with recovered COVID-19 (REB21-0035). The study was also registered at clinicaltrials.gov (MOIST late cross-sectional study; NCT04525404). All patients provided written informed consent. The Canadian VIGOUR Centre (thecvc.ca) helped provide project management, and the study team vouches for the data integrity and analyses of the study. Patient related variables were captured in REDCap (Research Electronic Data Capture) hosted at the University of Alberta and imaging data was stored in a secure server in the department of biomedical engineering at the University of Alberta. The principal investigator ([name]) oversaw site monitoring and data management and will supervise all analyses related to the study.

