### Sample size calculation

There is little data informing on associations between symptom burden, functional performance and MRI derived tissue composition in patients with recovered COVID-19. At the time of our study conception, only one MRI study reported on 100 patients at a median of 71 days from COVID-19 illness and found increased native myocardial T1 compared to 50 healthy controls, median 1,125 ms vs. 1,082 ms, respectively. They also reported increase myocardial T1 in those with prior hospitalization (*N* = 33) compared to patients who had recovered at home (*N* = 67), median 1,141 ms vs. 1,119 ms, *p* = 0.008 (16). A subsequent multicenter study of 148 patients with prior hospitalization for severe COVID-19 also found increased myocardial T1 compared to 40 healthy volunteers, mean 1,033 ms vs. 1,008 ms, *p* < 0.001 (17). However, data linking imaging to symptoms and functional performance is inconclusive. In a multi-organ, MRI based study of 201 patients with long COVID, only abnormalities in myocardial T1 were associated with severe symptom burden and/or disability (14). A multisystem, MRI-based study of 54 patients with prior hospitalization for severe COVID-19 found that imaging derived organ injury (cardiac, renal and hepatic T1 and brain T2*) was associated with circulating biomarkers of inflammation but not with functional performance (spirometry, 6MWT and cognitive testing) (13). Given the lack of data on potential associations of MRI tissue characterization with symptom burden and/or functional performance at the time, we empirically established a target of 200 patients with recovered COVID-19 and 100 age- and sex-matched healthy controls without prior infection. Clinical characteristics of the study population are presented in Table 3.

**Table 3 tab3:** Clinical characteristics.

	Recovered COVID-19	Healthy controls
Number of patients	215	133
Female, (%)	139 (65%)	68 (51%)
Age	51 (14)	47 (15)
Caucasian race, (%)	170 (79%)	113 (85%)
Height, cm	168 (10)	170 (9)
Weight, kg	83 (20)	72 (13)
Systolic blood pressure, mmHg	134 (18)	122 (13)
Diastolic blood pressure, mmHg	84 (11)	80 (9)
Heart rate, bpm	71 (12)	73 (13)
Oxygen saturation (%)	98 (2)	98 (2)

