**COVID-19 Illness**		
Duration of Illness		
1–7 days, (%)	80 (37%)	Not applicable
8–14 days, (%)	68 (32%)	
>14 days, (%)	67 (31%)	
Hospitalized, (%)	59 (27%)	
Intensive care unit, (%)	17 (8%)	
Ventilation, (%)	11 (5%)	

Values are represented as total number (%) or mean (standard deviation).

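### Controls called age- and sex-matched differ from patients on both in Table 3, and the stated patient-control tests are unadjusted, so age or sex differences can be read as COVID-19 organ injury

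*Protocol article*

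**What the plan says.** The Study design section describes the comparison group as "age- and sex-matched healthy control participants without prior COVID-19 infection". The Sample size calculation section repeats the claim: "we empirically established a target of 200 patients with recovered COVID-19 and 100 age- and sex-matched healthy controls without prior infection". No matching ratio, caliper, procedure or matched subset is given. Patients were recruited from October 2020 to July 2021 and controls from July 2021 to July 2023 (Participant selection).

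Table 3 reports the groups as enrolled, 215 patients and 133 controls, with this footnote on format: "Values are represented as total number (%) or mean (standard deviation".

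For patient-control comparisons of continuous measures, the Statistical plan names the "two sample t-test or Mann–Whitney U test used for continuous variables, as appropriate". Categorical measures get a chi-square or Fisher test. Neither carries covariates or uses pairing. The only adjustment named in the plan is in the multivariable Cox model, which tests parameters for their "association with composite outcome after adjustment for baseline risk". That model concerns clinical events, not the organ-injury contrast. The significance rule is "A *p* value less than 0.05 will be considered significant for all tests".

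The closing paragraph of the Introduction places the contrast with healthy controls inside the primary objective, beside the contrast between patients with more and fewer symptoms.

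**The concern.** An unadjusted two-group test is defensible for age and sex if the groups really are balanced on them. Here the text asserts balance, the table shows otherwise, and the tests neither adjust for the two variables nor use any pairing. Spirometry, walking distance, LVEF, tissue T1 and muscle measures can all depend on age, sex or body size. Where they do, part of a patient-control difference may reflect who was enrolled and not what infection did. A reader who trusts the matching label would have no reason to suspect this.

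**Working it through.** **Inputs.** From Table 3: female 139 of 215 patients and 68 of 133 controls; age 51 (14) and 47 (15) years. From the Statistical plan: significance level 0.05, taken as two-sided because the sidedness is not stated. The 200/100 target is described as empirical, so there is no sample-size formula to reproduce.

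**1. Reproduce the printed percentages.** 139/215 = 64.7% and 68/133 = 51.1%, which agree with 65% and 51%.

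**2. Sex balance.**
- Difference: 64.7 − 51.1 = 13.5 percentage points before rounding (95% CI 2.9 to 24.2).
- Chi-square without continuity correction = 6.24, p = 0.013; Fisher p = 0.014.
- Standardised difference: 0.135 / √[(0.647 × 0.353 + 0.511 × 0.489)/2] = 0.135/0.489 = 0.28.

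These come from exact counts, so rounding cannot explain them.

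**3. Age balance.**
- Difference: 4 years; standard error √(14²/215 + 15²/133) = 1.61; 95% CI 0.8 to 7.2.
- Welch t = 2.48, p = 0.014.
- Standardised difference: 4/√[(14² + 15²)/2] = 4/14.5 = 0.28.
- Over the rounding range of the printed means and SDs, the standardised difference runs from 0.20 to 0.36 and the Welch p from 0.0015 to 0.073.

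Both standardised differences exceed the customary balance threshold of 0.1, age included at the low end of its rounding range.

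**4. Effect on an unadjusted test when infection does nothing.** The documents give no age or sex effect on any metric, so these are assumptions: a sex difference *s* of 0.5 to 1.5 and an age correlation *r* of 0.2 to 0.4, in units of the metric's overall SD.

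Spurious difference *d* = 0.135 *s* ± 0.276 *r*, with plus if the two effects act in the same direction and minus if they oppose. The standard error of a standardised difference is √(1/215 + 1/133) = 0.110. Rejection rate = Φ(*d*/0.110 − 1.96) + Φ(−*d*/0.110 − 1.96).

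| *s* | *r* | *d*, same direction | Rejects | *d*, opposing | Rejects |
|---|---|---|---|---|---|
| 0.5 | 0.2 | 0.123 | 20% | 0.012 | 5% |
| 0.5 | 0.4 | 0.178 | 36% | −0.043 | 7% |
| 1.5 | 0.2 | 0.258 | 65% | 0.148 | 27% |
| 1.5 | 0.4 | 0.313 | 81% | 0.093 | 13% |

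The range is thus about 20% to 80% in the same direction and about 5% to 27% opposing. For scale, the difference detectable with 80% power at 215 against 133 is (1.96 + 0.84) × 0.110 = 0.31 SD, so the largest spurious difference is the size of an effect the study could just detect.

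**5. Does adjustment help?** In simulations of 4,000 runs per scenario, with age correlations up to 0.5 and sex effects up to 0.5 SD, linear regression on group, age and sex rejected 4.4% to 5.3% of the time. The unadjusted test rejected up to 46%.

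**6. What adjustment does not reach.** Cardiovascular disease and its risk factors were exclusions for controls only. Table 3 shows hypertension 24% against 0, diabetes 13% against 0 and dyslipidemia 18% against 0. With no affected controls, the data hold no control comparison for affected patients.

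**The case against.** Several points on the other side are sound and limit the claim.

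- **Not every metric will be biased.** A reader might infer that any age- or sex-dependent measure must differ between the groups. It need not: opposing effects can nearly cancel, as the first row of the table shows. The 80% figure also requires a large sex effect acting with age.
- **The primary objective is not undermined as a whole.** The hypothesis links MRI tissue injury to disability and function. The analyses that address it, across symptom groups within patients and by correlation with functional performance, are not affected by a patient-control imbalance.
- **Brain and cognitive metrics stand apart.** Participant selection says that normative brain imaging and cognitive data were collected separately before the pandemic. The documents do not say whether those people are among the 133, so the Table 3 imbalance cannot be carried over to those contrasts.
- **Weight is not evidence against the label.** Weight is 83 against 72 kg (standardised difference 0.65), but matching on body size is never claimed.
- **The age p-value is sensitive to rounding.** The sex imbalance is firm.

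Two defences fail. A matched subset could be drawn, since 133 controls were enrolled against a target of 100, but none is described. An unseen analysis plan could add covariates, but this text does not leave the method open: it names the unadjusted tests.

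**Conclusion.** Wrong as written. The matching claim, made twice, is contradicted by Table 3, and the tests fixed for the patient-control contrast neither adjust nor pair. Age and sex differences can therefore be read as COVID-19 organ injury in that contrast. The imbalance itself (standardised difference 0.28 for each variable) rests on the document's own figures. The size of the harm rests on the assumed effects and on whether they add or oppose, and it will vary by metric.

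It might also be inferred that adjusting for age and sex would allow a remaining difference to be attributed to infection. The documents do not support that, because the control-only cardiovascular exclusions leave a separate confounder in place.

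**What to change.** 1. Remove or correct the age- and sex-matched description in both sections. If a matched subset exists, document how it was formed.
2. Replace the unadjusted patient-control tests with regression of each metric on group, adjusted for at least age and sex, and for body size where it is not part of the outcome. Report adjusted differences with 95% CIs.
3. Add a sensitivity analysis restricted to patients without the cardiovascular disease and risk factors that were excluded in controls. State that covariate adjustment cannot separate those factors from COVID-19.
4. For brain and cognitive metrics, check age and sex balance against the separate pre-pandemic cohort, and adjust using that cohort's own data.

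**Cost.** Table 3 already reports age, sex, height and weight for both groups, and the Statistical plan is written in the future tense, so items 1 and 2 need wording and a little more analysis. Item 4 needs the normative cohort's age and sex data.

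Item 3 loses precision. Suppose the restriction covers the hypertension, diabetes, dyslipidemia, coronary disease, heart failure, atrial fibrillation and stroke rows of Table 3. Between 51 patients (full overlap with hypertension) and 51 + 28 + 38 + 4 + 1 + 4 + 5 = 131 patients (no overlap) would drop out, leaving 84 to 164. The standard error would rise from 0.110 to between √(1/164 + 1/133) = 0.117 and √(1/84 + 1/133) = 0.139, that is by about 6% to 26%.
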